### Sample size and dosage

Secondary purposes will be investigated within the frames of a feasibility study that include, as a corollary, the recruitment of a relatively small sample size to have preliminary data to determine whether interventions and research procedures are appropriate, acceptable, and practical [61].

Therefore, conclusions regarding mental health clinical endpoints as well as the therapeutic relationship and the role of music technology will be interpreted with care and presented as preliminary. Presently, positive results regarding the effectiveness of MT, as compared to a ST provided by the community, reflecting an improvement in the mental health of SUD participants have not been reported yet; for this reason, notwithstanding the small sample size limitation, it is essential to fill this gap in the literature. Additionally, analysis of the primary and secondary study aims will be performed on an intention-to-treat basis to manage drop-outs and missing data. A total of 6 IMT and GMT sessions will be offered. Patients with fewer sessions will not be excluded from data analysis (intention-to-treat principle; [62]). Nevertheless, to minimize missing data imputation, for participants not attending the post-treatment test battery at week 8, the last observation carried forward (i.e., in this case, baseline measurements at week 1) will be used.

Whilst depressive [26, 27], anxiety [26, 28, 29] and craving [30–32] symptoms have been shown to improve after MT in individuals with SUD, this will be a first attempt to study these dimensions in a community setting by measuring their neural correlates.

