**Methods:**

Fifteen participants, from a community service based in London, will take part in a mixed-methods non-blind randomized-controlled trial. Ten participants will receive six-weekly sessions of music therapy in addition to the standard treatment offered by the CSMTS—five of them will receive individual music therapy and five of them will receive group music therapy—while a further five participants will act as a control group receiving standard treatment only.

Satisfaction and acceptability will be evaluated in focus groups with service users and staff members following the final treatment session. Moreover, attendance and completion rates will be monitored throughout the intervention. Subjective and behavioral indexes will be assessed before and after the interventions to explore the effects of music therapy on craving, substance use, symptoms of depression and anxiety, inhibitory control, and will be correlated with associated neurophysiological signatures. In-session analysis of two individual music therapy sessions will serve to explore how music and emotion are processed in the brain within the therapy. The data collected at each step will be included in an intention-to-treat analysis basis.

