### Participants

Fifteen SUs and, from a minimum of 4 to a maximum of 8 staff members, will be recruited from WDP. In total, we will recruit between 19 and 23 participants. The inclusion criteria for the recruitment of SUs include: (I) being a SU in structured treatment for drug and/or alcohol misuse, (II) being 18 years old or older, (III) reporting symptoms of depression and/or anxiety, (IV) being deemed suitable to take part in a group/individual setting by their key workers (who are Recovery Practitioners responsible for coordinating and delivering psychosocial interventions for SUs), (V) being right-handed.

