### Outcome measures for each participant (GMT, IMT and CG)

In this section, we describe mental health, substance use and craving measures that will be administered prior to (baseline) and after (post-intervention) the intervention; therefore, at week 1 and week 8. To measure participants’ depressive symptoms, the Patient Health Questionnaire (PHQ-9) will be completed, and a resting-state EEG frontal alpha asymmetry (FAA) will be measured. The PHQ-9 is a validated and commonly used self-report to screen for depressive symptomatology [37] and shows a good internal consistency when administered to participants with SUD (Cronbach’s α = 0.90; [38]). The FAA is a neural biomarker representing the difference between the left and right alpha activity over the frontal regions of the brain [39] and a reduced FAA has been associated with depressive symptomatology [40, 41]. To measure participants’ anxiety symptoms, the Generalized Anxiety Disorder-7 (GAD-7) questionnaire will be completed and resting-state EEG frontal midline theta (FMT) will be measured. The GAD-7 is a validated [42] and standardized [43] self-report to screen for anxiety symptomatology showing a good internal consistency when completed by SUD participants (Cronbach’s α = 0.91; [43]). FMT is a neural biomarker that has been associated with anxiety [44] and increased resting-state FMT positively correlated with the reduction of anxiety after an MT intervention for clients with depression [16]. To measure participants’ feeling of craving in the preceding 24 h, the Brief Substance Craving Scale (BSCS) questionnaire will be completed and resting-state EEG beta frequency band will be measured. The BSCS is a validated questionnaire to assess craving in the SUD population over a period of 24 h [45]. The EEG beta frequency band is a neural EEG rhythm suggested to play a role in processing abstinence-related and cue-induced craving [46]; indeed, increased resting-state beta frequency band activity in the dorsal anterior cingulate cortex and pregenual anterior cingulate cortex have been associated with craving [46]. After the resting-state EEG recordings, participants will complete a behavioral Go/No-Go task while EEG event-related potentials (ERPs) will be measured to assess inhibitory control. The visual Go/No-Go task is a straightforward behavioral paradigm requiring participants to respond with a button press when a set of stimuli are presented (circles appearing at the top right and bottom left corners of the screen) and to withhold the response when another set of stimuli, with the same probability of occurrence, is presented (circles appearing at the top left and bottom right corners of the screen) [47–49]. To measure substance use, days of primary substance used, usage of primary substance per day, physical wellbeing, mental wellbeing and overall quality of life, the Treatment Outcome Profile (TOP) questionnaire will be completed. The TOP is a psychological health scale validated in a sample of SUD participants [50] and a standard measurement tool used in community treatments services in England and Wales. Biomarkers, such as Urine Drug Screening (UDS) or breathalyzers, will not be used during this feasibility study. This is due to costs and added burdens to the participants and the hosting service. While the TOP is a self-reported measure, it is a questionnaire regularly administered to all service users and we expect it to provide indicative results of which can be followed up in further studies.

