
For the resting-state EEG data (alpha—FAA -, beta, and theta—FMT—bands) pre-post intervention comparisons will be performed utilizing z-scores from a Normative EEG database (NG software) [54]. Furthermore, to represent the pre-post intervention difference in the topographic distribution of EEG power in the selected frequency bands a paired-samples t-test will be performed for each of the three groups. If deviations from normality will be found in the data, a non-parametric Wilcoxon Signed-Rank test will be performed. Between-group power differences will be calculated as well, by comparing differences in the topographic distribution of the EEG power in participants who received MT (GMT and IMT) alongside ST vs participants who received ST only through an independent t-test. If deviations from normality will be found in the data, a non-parametric Mann–Whitney test will be performed. Relationships between changes in the pre-post intervention questionnaire scores (PHQ-9, GAD 7, BSCS, VAS, HAQ-II) and changes in the respective EEG measures (see above) will be tested using Pearson's correlation coefficients with 95% confidence interval [16]. Likewise, we will implement the same correlation procedure to test the relationship between pre-post intervention changes in inhibitory control (P3 ERP amplitude and accuracy on “no-go” trials) and changes in the scores of the Brief Substance Craving Scale. Changes in the pre-post MT (GMT and IMT) sessions scores from the craving thermometer will be analyzed graphically (i.e., scatterplot). Those who attend more than two sessions but disengage before the study ends will have the measures up to the point of their disengagement included in data analysis.

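### Carrying the week-1 value forward puts invented zero-change pairs into the change-change correlations, pulling them in the expected direction if both measures shift and several people miss week 8

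*Protocol article*

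**What the plan says.** The rule stands in the Discussion of the protocol article, under Sample size and dosage. It states that "analysis of the primary and secondary study aims will be performed on an intention-to-treat basis to manage drop-outs and missing data". It then fixes that "the last observation carried forward (i.e., in this case, baseline measurements at week 1) will be used", and it applies this "for participants not attending the post-treatment test battery at week 8". The stated purpose is to keep imputation to a minimum.

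The battery has two time points, "therefore, at week 1 and week 8" (Outcome measures for each participant; Table 1 agrees). It covers PHQ-9, GAD-7, BSCS, TOP, resting-state FAA, FMT and beta, and the Go/No-Go task with its P3.

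Analysis strategy regarding the secondary study aims puts the changes to two uses:
- "Relationships between changes in the pre-post intervention questionnaire scores" and changes in the matching EEG measures are tested by Pearson correlation with 95% confidence intervals. The same is done for inhibitory control against BSCS.
- Difference scores in the MT groups are compared with those in the ST group by an independent t-test or Mann–Whitney test.

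That section also says that people who attend more than two sessions and then disengage contribute their measures up to that point. It does not mention imputation.

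**The concern.** With one pre and one post measurement, the last observation is always the baseline. The rule is therefore a single imputation of no change, applied to all battery measures together and with no allowance for uncertainty. That sits badly with its stated purpose.

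The usual defence is that carrying baseline forward is conservative because it dilutes effects. That does not hold for a correlation of two change scores. If attenders cluster away from the origin on both axes, extra points at the origin stretch the cloud along the line joining the two groups. A correlation appears even if individual symptom change and individual EEG change are unrelated. The section on neural correlates expects both members of each pair to move: PHQ-9 down with FAA up, GAD-7 down with FMT up, BSCS down with beta down, BSCS down with NoGo P3 and accuracy up. The induced correlation is negative where the two move in opposite directions and positive for BSCS with beta. In each case it has the sign that the hypothesis implies.

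At stake are the preliminary findings on mechanism and the preliminary arm differences that the authors want as a base for a larger trial.

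**Working it through.** **Inputs from the protocol.** "Fifteen SUs and, from a minimum of 4 to a maximum of 8 staff members, will be recruited from WDP", so there are 15 service users. Of the ten in MT, "five of them will receive individual music therapy and five of them will receive group music therapy", and five are controls. The analysis is by intention to treat, and absentees get a change of 0. The protocol gives no power, alpha, dropout or effect-size figure, so there is no calculation to reproduce.

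**Assumptions.** Two-sided 5% tests; 1, 3 or 5 of 15 missing, unrelated to outcome; normal change scores; mean changes of 0, 0.5, 1 or 1.5 SD on both measures in opposite directions; true correlation 0. Some loss is foreseen: Recruitment lets group therapy continue while 3 participants remain and provides for replacing individual-therapy dropouts.

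**Formula.** Let a fraction d sit at (0,0), and let attenders have correlation ρ and mean changes m_x, m_y in SD units. Then

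r = (ρ + d·m_x·m_y) / √[(1 + d·m_x²)(1 + d·m_y²)].

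For ρ = 0:
- d = 3/15, shifts of −1 and +1: −0.2/1.2 = −0.17
- d = 3/15, shifts of −1.5 and +1.5: −0.45/1.45 = −0.31
- d = 5/15, shifts of −1 and +1: −0.333/1.333 = −0.25

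**Simulation at n = 15.** Entries are mean signed r, then the false-positive rate.

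| Mean shift | 1 missing | 3 missing | 5 missing |
|---|---|---|---|
| 0 | 0.00; 6% | 0.00; 8% | 0.00; 11% |
| 0.5 SD | −0.02; 5% | −0.06; 7% | −0.09; 11% |
| 1 SD | −0.07; 5% | −0.19; 10% | −0.28; 19% |
| 1.5 SD | −0.15; 6.5% | −0.34; 22% | −0.46; 43% |

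The simulated means are slightly larger than the formula gives because n is small. With no mean shift r is unbiased, but the test still rejects too often because invented pairs are counted in n. With 3 missing and shifts of 1 SD, the 95% interval covers the true value 89% of the time; at 1.5 SD, 77%. Using observed pairs only, mean r is 0.00, false positives are about 5% and coverage is about 95% in every one of these scenarios.

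**Arm difference.** The expected carried-forward difference is (1 − f_MT)·m_MT − (1 − f_ST)·m_ST, where f is the missing fraction and m the mean change.
- Equal missingness, true difference −1 SD (MT changes, ST does not): 0.8 × (−1) = −0.80 at 20% missing, and −0.60 at 40%.
- Both arms improve 1 SD, 4 of 10 MT and 0 of 5 ST missing: −0.6 − (−1) = +0.40 SD, against MT (12% false positives).
- Both arms improve 1 SD, 0 of 10 MT and 2 of 5 ST missing: −1 − (−0.6) = −0.40 SD, in favour of MT (9% false positives).

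If neither arm changes over time, there is no bias.

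**The case against.** **The harm is conditional.** A reader might infer that the rule manufactures the correlations sought. The documents do not support that. They give no dropout rate and no effect size. With one absentee the effect is negligible, and a shift in r needs mean change on both measures. This limits the size of the problem but does not make the rule sound.

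**Pooling may matter as much.** The protocol does not say whether the correlations pool the arms. Suppose they do, and only the ten MT participants move by 1 SD. Complete data then already give mean r of about 0.19 in size and 10% false positives. With three missing, observed pairs give 0.19 and 9%, while carrying forward gives 0.25 and 17%. In that reading only part of the excess comes from the imputation, so observed pairs alone are not enough. This stands and shapes the fix.

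**Observed data do not cure outcome-related dropout.** Suppose attenders improve 4 points, leavers worsen 2, and 40% of MT and 20% of ST are missing.
- True difference: (−2.4 + 0.8) − (−3.2 + 0.4) = −1.6 − (−2.8) = +1.2
- Carried forward: −2.4 − (−3.2) = +0.8
- Observed only: −4 − (−4) = 0

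Here observed data do worse than the planned rule. Sensitivity analyses are therefore essential.

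**Three further inferences fail.**
- A Wilcoxon test that drops zeros is not harmed, since what remains is the observed pairs.
- The rule does not hide week-8 completeness. Nothing in it prevents missing counts from being reported, and attendance and completion are monitored.
- A missed TOP is not shown to be recoverable. The protocol says that "it is a questionnaire regularly administered to all service users", not that a record exists at week 8.

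**Secondary results are labelled preliminary,** and the primary feasibility analysis is descriptive and thematic. That lowers the consequence. The label warns of imprecision, however, and not of a pull in one direction.

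**Conclusion.** The concern holds in limited form. The rule is a single imputation of no change and should not feed the change-change correlations. With 3 of 15 missing and a true correlation of 0, it produces a mean r of about 0.06 to 0.34 in size and 7% to 22% false positives for shifts of 0.5 to 1.5 SD. With 5 missing the figures are 0.09 to 0.46 and 11% to 43%. With 1 missing the effect is small. These figures assume missingness unrelated to outcome and the same shift in everyone who attends.

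Arm differences are attenuated under equal missingness. Under unequal missingness they can be biased either way when the arms change over time.

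The problem is confined to the week-1/week-8 battery. The craving thermometer and HAQ-II are tied to sessions and have no week-1 value to carry. Participants who ask for their data to be destroyed are also outside the rule. The primary feasibility conclusions do not depend on it. The rule should be changed before analysis, but it does not invalidate the study.

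**What to change.** 1. Use only observed pre-post pairs in all change-change correlations. Do not pool MT and ST participants in them without allowing for arm.
2. For arm comparisons, make observed week-8 data adjusted for baseline the main analysis. For the questionnaires, show baseline carried forward and a scenario in which absentees worsen, both labelled as sensitivity analyses.
3. Report the number missing at week 8 per arm and per measure.
4. Reconcile the statement about measures up to disengagement, in Analysis strategy regarding the secondary study aims, with the carry-forward rule in Sample size and dosage, and remove the claim that the rule minimises imputation.

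The cost is a few sentences and one small table, with no new measurement. The downside is that the analysed n falls by the number missing, so intervals widen. That reflects the information actually collected.

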### Neural correlates and corresponding outcomes related to craving and mental health

Specifically, we expect to provide preliminary positive results regarding a reduction in depressive symptomatology after an MT intervention, as indicated by lower scores on the Patient Health Questionnaire—9 [37] and increased resting-state FAA (higher left-sided frontally distributed power in alpha range [40, 41]); a reduction in anxiety symptomatology after an MT intervention, as indicated by lower scores on the Generalized Anxiety Disorder assessment—7 [42] and increased resting-state FMT [16, 44] and a reduction in short-term craving symptomatology after an MT intervention, as indicated by lower scores at the Brief Substance Craving Scale [45] and reduced power in the beta frequency band measured at rest [46]. The neural correlates of depressive, anxiety and craving symptomatology will be measured by means of resting-state EEG to investigate the intrinsic activity [63] of the brain and utilizing neurometric comparisons against a normative EEG database [16, 54]. In this way, we can examine the relationship between pre-post intervention changes in the multi-item questionnaires scores and pre-post intervention changes in the neural activity that is hypothesized to underpin depressive, anxiety and craving symptomatology. Since the experience of craving is related to a lack of control over intrusive drug-related thoughts [64, 65] and lack of behavioral control [66, 67], it can be approached with behavioral tasks requiring the deployment of inhibitory control functions (e.g., response inhibition) [11, 64]. The effect of MT on inhibitory control will be assessed using a behavioral task (Go/No-Go task), changes in the EEG event-related potential P3 and by measuring the correlation between inhibitory-related measures and short-term craving measures. It is expected to provide preliminary positive results regarding an improvement in inhibitory control after an MT intervention, as indicated by a higher accuracy in the Go/No-Go task and increased NoGo P3 event-related potential [47–49]. Furthermore, we expect a negative correlation between inhibition indexes (increased pre-post intervention NoGo-P3 brainwaves and higher pre-post intervention accuracy on NoGo trials) and scores in the BSCS. In other words, it is expected that an improvement in inhibitory control skills after an MT intervention would be associated with decreased subjective feeling of craving. A second measure to assess craving will be used. Since music represents an environmental cue, it can be associated with the drug experience and, potentially, induce craving by triggering emotional memories [68, 69]. Therefore, to monitor for instances of addiction memories that can possibly induce craving [15], an instantaneous single-item measure of craving will be collected before and after group and individual music therapy sessions. While MT has been suggested to reduce craving [30–32], the element of music itself, in some circumstances, can determine the induction of a craving state [68, 69] and there is no systematic empirical evidence about the mechanisms underlying the rising of moments of craving in MT sessions [4].

### Process related outcomes and analysis

For this reason, we have been implementing a close monitoring for instances of addiction memories and potential peaks of craving to study if, how and when these instances occur. Working with a qualified music therapist, individuals can begin to experience non-drug induced emotions through the exploration and re-creation of preferred music pieces that were originally linked to drug-induced emotional experiences and opening up new pathways of emotional exploration [70, 71]. This treatment perspective, through retraining and reframing emotional intensity, builds on gradually decreasing and recalibrating the emotional impact related to music-induced memories [15]. Moments of state-dependent recall, during which individuals may experience cravings or urges relating to their drug use offer music therapists an opportunity to work with individuals towards retraining and reframing musical cues. Understanding how the therapist recognizes these moments can provide important insight into the therapeutic process. To investigate this, we will administer a craving thermometer pre-post MT session, a post MT session debriefing with the therapist and a more intense feasibility investigation, including a post-session questionnaire (HAQ-II) and dual-EEG with video session monitoring (to revisit instances) during IMT sessions 2 and 5. With EEG hyperscanning and HAQ-II we aim to monitor and investigate the neural dynamics of emotional processing deploying within the MT process with the use of music technology. During these two IMT sessions, we will test the feasibility of using EEG hyperscanning and AV monitoring to examine the neural correlates of therapeutically relevant moments involving craving, intense emotion, and therapeutic interpersonal interaction, and we expect that these moments will occur more frequently in the later sessions. This research approach has already been shown to provide valuable insights into the neural dynamics of shared emotional processing during a music therapy session [22]. By segmenting the EEG data corresponding to therapeutically important moments of the audio–video recorded therapy session (such as moments regarding craving and intense emotions, as determined from post-session interviews with participants and by observations from the therapist), we plan to analyze and contrast these segments with moments not selected as pivotal or emotionally relevant (i.e., moments of non-interest). Furthermore, we will record and analyze participants’ engagement with electronic music production instruments (EMPI) and acoustic instruments. With this methodological approach, we can explore facets of therapeutic alliance that is considered a non-specific factor and a central element of any kind of psychotherapy, MT, and art therapy [72, 73] by analyzing temporal dynamics of contextualized events and therapeutically relevant moments [21, 22].
